#### Dropouts and missing data

Reasons for dropouts will be documented and reported. If patients are alive and missings are assumed to be missing at random (MAR), we will use multiple imputation methods based on ten imputed data sets [25] with multiple imputation by chained equations (MICE).

### Module 2: secondary data, claims data from health insurance funds

#### Design and participants

Another part of the OSCAR evaluation involves analyzing claims data from the BKK health insurance funds. In contrast to the patient-reported parameters in Module 1, the claims data will make it possible to analyze objective parameters. This kind of data is a valid and relevant source, and has been used in many healthcare research projects in Germany. The data from Modules 1 and 2 will not be linked. If available, the secondary data will be analyzed for the period up to 12 months before and after enrollment.

#### Inclusion and exclusion criteria

This data is only available for the patients in the intervention group, who have health insurance with BKK (*n* = 150). A new, independent and anonymous control group will therefore be drawn from BKK-insured patients who did not take part in the OSCAR intervention (*n* = 600). All included patients must meet the inclusion and exclusion criteria mentioned above. Furthermore, the patients in the control group should be treated in hospitals comparable to those where the patients in the intervention group were treated. In addition, the control group will be matched with the intervention group by age, gender, and diagnosis.

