#### Variables

The following aspects are of interest: time-to-death, all costs of treatment, and the incidence rate of hospitalization and outpatient visits.

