#### Statistical analysis plan

Paired t-test or Wilcoxon signed rank test will be performed to compare the costs of treatment per month. The generalized estimating equation (GEE) for Poisson regression will be applied to compare the incidence rate of hospitalization and outpatient visits between intervention and matched controls. Kaplan-Meier curve and Cox regression analysis will be performed to compare time-to-death between the groups.

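### Module 2 obtains up to a year of pre-enrolment claims but does not say how they enter the group comparison, so differences in prior cost, hospital use or disease phase are controlled only in part

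*Protocol article*

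**What the plan says.** All references are to the Protocol article.

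- **Module 2, Inclusion and exclusion criteria.** Claims exist for one Module 1 arm only: "This data is only available for the patients in the intervention group, who have health insurance with BKK" (n = 150). Hence "A new, independent and anonymous control group will therefore be drawn from BKK-insured patients who did not take part in the OSCAR intervention" (n = 600). Three restrictions shape that group: "All included patients must meet the inclusion and exclusion criteria mentioned above"; "the patients in the control group should be treated in hospitals comparable to those where the patients in the intervention group were treated"; and "the control group will be matched with the intervention group by age, gender, and diagnosis".
- **Module 2, Design and participants.** If available, "the secondary data will be analyzed for the period up to 12 months before and after enrollment".
- **Module 2, Variables.** The outcomes are "time-to-death, all costs of treatment, and the incidence rate of hospitalization and outpatient visits".
- **Module 2, Statistical analysis plan.** Monthly costs are compared by a paired t-test or Wilcoxon signed rank test, and event rates by a Poisson GEE. For survival, "Kaplan-Meier curve and Cox regression analysis will be performed to compare time-to-death between the groups". No baseline measure, covariate or time origin is named for any of these.
- **Discussion.** Matching is given as the means of bias control for Module 2. The propensity score with inverse probability weighting is described for Module 1.

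**The concern.** OSCAR patients were approached in hospital by a Social Care Nurse and agreed to join a programme that the Background section aims at advanced disease with poor prognosis. The eligibility rule is wider: adult age and a combination of a cancer code and a procedure code. As printed, it has no criterion for stage, prognosis or time since the procedure. Two patients with the same age, gender and diagnosis can both satisfy it while being in quite different phases of disease.

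Prior cost and prior hospital use are the most direct markers of disease phase that claims contain, and they are likely to predict later cost and use strongly. The plan obtains them, but the methods it lists compare the groups without them. If the groups differ at the start, part of that difference will appear after enrolment and can be read as an effect of OSCAR on cost, hospitalisation or death. A real effect could equally be hidden.

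**Working it through.** Module 2 states no power or precision figure, so there is none to reproduce. The check is a reading of the text followed by an illustration of size.

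**1. Where the pre-period data could enter.**

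| Stage | What the article names | Prior cost or use included? |
|---|---|---|
| Selecting controls | eligibility codes, comparable hospitals | no |
| Matching | age, gender, diagnosis | no |
| Cost test | paired t or signed rank on monthly cost | not stated |
| Rates | Poisson GEE, intervention versus matched controls | not stated |
| Survival | Kaplan-Meier, Cox | not stated |

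The paired test could be read as before versus after within patients. The Study objectives section, however, sets the aim as comparing costs between the two groups, which favours matched sets. A before-after test within one arm would not answer that objective.

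**2. Size of the bias on cost.**

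*From the article:* n = 150 and n = 600.
*Assumed:* pre-period imbalance Δ = 0.2 SD; pre/post correlation r = 0.5 (range 0.4 to 0.6); equal SD in both periods; no true OSCAR effect.

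- Bias of an unadjusted post-period comparison = r × Δ = 0.5 × 0.2 = 0.10 SD.
- Standard error, independent groups = √(1/150 + 1/600) = √0.008333 = 0.0913 SD.
- Standardised bias = 0.10 / 0.0913 = 1.095.
- False-positive rate = P(Z > 1.96 − 1.095) + P(Z < −1.96 − 1.095) = 0.194 + 0.001 ≈ 0.195, against a nominal 0.05.

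Over the assumed range of r:

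| r | Bias (SD) | Bias / SE | False-positive rate |
|---|---|---|---|
| 0.4 | 0.08 | 0.88 | 14% |
| 0.5 | 0.10 | 1.10 | 19% |
| 0.6 | 0.12 | 1.31 | 26% |

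Halving the imbalance to 0.1 SD at r = 0.5 gives 0.05 / 0.0913 = 0.55 SE and a rate of about 8.5%.

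**3. Does the planned pairing change this?** There are 600/150 = 4 controls per case. Let ρ be the within-set correlation. The variance of a case minus the mean of its four controls is σ²[1 + (1 + 3ρ)/4 − 2ρ] = 1.25σ²(1 − ρ). Over 150 sets the standard error is √(1.25(1 − ρ)/150) = 0.0913 × √(1 − ρ) SD. At ρ = 0 this equals the independent-groups value, and for ρ > 0 it is smaller. For a given imbalance, the independent-groups figure therefore does not exaggerate the problem.

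**4. Mortality, illustration only.** A Cox model was simulated with true hazard ratio 1, 12 months of follow-up, median survival 24 months in non-severe disease and a severity hazard ratio of 2 to 3. Severe disease was assumed in 50 to 70% of OSCAR patients and 40% of controls. The unadjusted hazard ratio was about 1.06 to 1.38. With the shares exchanged it would be roughly the reciprocal, 1/1.06 = 0.94 to 1/1.38 = 0.72. The sign comes from the assumption; the article does not supply it.

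**5. Gain in precision.** Adjusting for prior cost reduces residual variance by r²: 0.4² = 16% to 0.6² = 36%.

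**The case against.** The strongest reply is that this is an article, and that model covariates, the index date and the time origin are details usually left to a full protocol or analysis plan. That is a fair limit, and it means no bias has been demonstrated. It does not dispose of the point. The article states which variables are matched, gives matching as the Module 2 safeguard, and lists its tests. Matching variables decide which controls are drawn, and they are harder to repair later than a model term.

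Three further objections stand and narrow the point.

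- The restrictions go beyond the three matching variables. Shared ICD/OPS eligibility and comparable hospitals also act on severity. The code list is in Additional file 1, which is not shown, so how far diagnosis captures metastatic disease cannot be judged.
- A reader might infer that no analysis will use the pre-period. The article says those data will be analysed. What is missing is how they enter the between-group comparison.
- A reader might also infer that survival is biased in favour of OSCAR, because its patients had to live long enough to enrol. That requires the clock to start at diagnosis or procedure, which appears nowhere in the article. The only anchor given is enrolment, and from that anchor OSCAR patients have no guaranteed survival time. The control index date is unstated, not shown to be wrong.

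Module 2 also serves secondary aims: the article tests all secondary hypotheses in an exploratory framework, and time-to-death is not among the listed objectives. This lowers the stakes, but an exploratory cost comparison still has to be interpretable.

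**Conclusion.** The point holds in limited form. Followed as written, Module 2 compares costs, use and mortality with partial control of severity and no stated use of the prior-year claims, probably the best confounder information it has. On the assumed inputs (0.2 SD imbalance, correlation 0.4 to 0.6), the false-positive rate for cost would be about 14 to 26%, with 19% at the central value. If the matching and restrictions happen to balance prior cost, the excess disappears. The net direction cannot be derived from the article, and the text does not support a claim that severity or time zero is wholly uncontrolled. This should be settled before the controls are extracted, but it does not touch the primary quality-of-life comparison.

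**What to change.** In Module 2, Inclusion and exclusion criteria and Statistical analysis plan:

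1. Match on, or adjust for, total cost and hospital days in the 12 months before the index date.
2. For costs and counts, name one main model: baseline-adjusted, or group-by-period difference-in-differences. They rest on different assumptions. In the illustration above, baseline adjustment removes the bias, whereas a simple change score would leave (r − 1) × Δ = (0.5 − 1) × 0.2 = −0.10 SD. If prior differences are instead stable over time, the difference-in-differences is the natural choice. The other model can serve as a sensitivity analysis.
3. Put the same pre-index variables in the Cox model as covariates.
4. Because enrolment is not defined for controls, give each control its matched case's index date. Require the control to be alive and BKK-insured on that date, and start all windows and the survival clock there.
5. Report balance of prior cost and hospital days after matching, and say what is done where the prior year is incomplete, since these data are promised only if available.

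The cost is a changed extraction rule, the loss of some potential controls and slightly more complex models. No new data source is needed. Some confounding by features that claims do not record will remain and should be acknowledged.

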#### Variables

The following aspects are of interest: time-to-death, all costs of treatment, and the incidence rate of hospitalization and outpatient visits.

#### Statistical analysis plan

Paired t-test or Wilcoxon signed rank test will be performed to compare the costs of treatment per month. The generalized estimating equation (GEE) for Poisson regression will be applied to compare the incidence rate of hospitalization and outpatient visits between intervention and matched controls. Kaplan-Meier curve and Cox regression analysis will be performed to compare time-to-death between the groups.

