### Study objectives

Primary objective:

To compare quality of life over study period between the intervention group (patients who had met an SCN) and the control group (Module 1).

Secondary objective:
To compare the health literacy, participation, and physician-patient communication in the intervention and control groups (Module 1)To explore the associations between quality of life and health literacy, participation, and physician-patient communication (Module 1)To compare the incidence rate of outpatient visits in both groups (Modules 1 and 2)To compare the healthcare costs in both groups (Module 2)To assess the SCN’s practical experiences (Module 3)

### Inclusion and exclusion criteria for participation in the evaluation survey in modules 1 and 2

Inclusion criteria:
Aged ≥18 yearsAt least a combination of one type of cancer and one operation and procedure, as defined by the ICD and OPS codes listed in Additional file 1

Exclusion criteria:
Advanced dementiaAcute addictions

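### The Module 2 cost comparison names one-to-one pair tests for 150 patients and 600 matched controls, with no rule for reducing each matched set to one difference

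*Protocol article*

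**What the plan says.** The protocol article lists cost as a secondary objective that compares the groups: "To compare the healthcare costs in both groups (Module 2").

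Under Module 2, Inclusion and exclusion criteria, the intervention group has 150 patients: "This data is only available for the patients in the intervention group, who have health insurance with BKK (*n* = 150"). The comparators are "drawn from BKK-insured patients who did not take part in the OSCAR intervention (*n* = 600"), and "the control group will be matched with the intervention group by age, gender, and diagnosis". No matching ratio is given in words.

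Under Module 2, Statistical analysis plan, the cost method is: "Paired t-test or Wilcoxon signed rank test will be performed to compare the costs of treatment per month". For the count outcomes the next sentence names a different kind of method: "The generalized estimating equation (GEE) for Poisson regression will be applied to compare the incidence rate of hospitalization and outpatient visits between intervention and matched" comparators. The article does not say that one control is picked per patient, that control costs are averaged within a set, or when the t-test gives way to the signed-rank test.

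**The concern.** A paired t-test and a signed-rank test each take a single list of independent differences. With 150 values on one side and 600 on the other there is no such list until someone decides how to make it. The article fixes the test and the group sizes but not the step that connects them, and the possible steps have very different properties. One wastes data, one gives false precision, and one works for the t-test but not for the signed-rank test.

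The last case matters most in practice. Costs are usually right-skewed, and the signed-rank alternative is the one an analyst would be inclined to choose when they are. A spurious cost effect, or a needlessly imprecise one, would then enter the assessment of whether the programme should be extended to the wider healthcare system.

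**Working it through.** The article gives no power, effect size or SD for cost, so there is no Module 2 figure to reproduce.

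**Inputs from the article (Module 2, Inclusion and exclusion criteria).** 150 intervention patients and 600 matched controls. 600/150 = 4 controls per patient; this ratio is inferred.

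**Assumptions.** Equal cost variance s² in both groups; the same correlation r between any two members of a matched set; nominal two-sided 5%.

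**Route A: one control per patient.**
- Variance of the mean difference with 1:1 pairs: 2s²(1 − r)/150.
- Variance with all four controls: s²[1 + (1 + 3r)/4 − 2r]/150 = 1.25s²(1 − r)/150.
- Ratio: 2/1.25 = 1.6, whatever the value of r. Standard error ratio: √1.6 = 1.26.
- Controls unused: 600 − 150 = 450, or 75%.

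This route is valid but inefficient.

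**Route B: 600 pairs treated as independent, each patient used four times.**
- Variance the test would assume: 2s²(1 − r)/600.
- True variance: 1.25s²(1 − r)/150.
- Ratio: (1.25/150)/(2/600) = 2.5. Equivalently, two differences that share a patient correlate 0.5, so the design effect is 1 + 3 × 0.5 = 2.5.
- Type I error: 2[1 − Φ(1.96/√2.5)] = 0.215.

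**Route C: each patient minus the mean of that set's four controls.** This gives 150 independent differences, so the paired t-test is usable. The signed-rank test also needs those differences to be symmetric about zero under the null. One skewed value minus one exchangeable skewed value is symmetric; one skewed value minus a mean of four is not.

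**Simulation under no cost effect.** 150 sets of one patient and four controls, 2,000 runs per setting, lognormal costs. Log-SDs of 0.5, 1.0 and 1.5 are assumed, each with a set-level log-SD of 0 or 0.5. Each cell gives the rejection rates (nominal 5%) at set-level log-SD 0 and 0.5.

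| Log-SD | A: t-test | A: signed-rank | B: t-test | B: signed-rank | C: t-test | C: signed-rank |
|---|---|---|---|---|---|---|
| 0.5 | 5.9%, 4.8% | 6.0%, 5.2% | 22.6%, 22.8% | 22.6%, 20.8% | 6.3%, 4.2% | 18.4%, 19.8% |
| 1.0 | 4.0%, 4.0% | 4.2%, 5.0% | 21.5%, 22.4% | 19.3%, 21.0% | 5.4%, 6.4% | 52.6%, 53.0% |
| 1.5 | 4.0%, 3.8% | 5.2%, 4.8% | 20.0%, 22.0% | 19.8%, 20.0% | 7.4%, 6.6% | 79.2%, 80.0% |

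The Monte Carlo standard error near 5% is √(0.05 × 0.95/2000) = 0.5 percentage points. The t-test in Route C is therefore near nominal and slightly liberal at the heaviest skew. The signed-rank test in Route C fails at every skew tried.

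**The case against.** The best defence is that a sensible analyst would average the controls within each set and run a paired t-test, which uses all 600 controls and holds its error rate approximately. That stands. It would be wrong to say that no pair test can be applied to this design. But the article does not state the averaging step, and the step does not rescue the signed-rank alternative, which is named on equal terms with no rule for choosing between the two.

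A reader might infer that the plan carries a 21.5% false-positive rate. The article does not support that: nowhere does it say that patients will be reused in 600 independent pairs. The figure applies only if that route were taken.

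Four controls per patient is also an inference. The article speaks of matching one group with the other and gives no ratio; reading 600 as a pool from which matches are drawn is possible, though less natural. On that reading a 1:1 pair test would fit, but the article would have to say so.

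A third defence is that the pairing is before versus after within a patient, since Module 2, Design and participants, allows claims data from the year on either side of enrolment. The cost sentence names no groups, so its wording does not exclude this. Such a test would not, however, answer the stated objective, which compares costs between the groups.

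Finally, one might extend the criticism to survival: "Kaplan-Meier curve and Cox regression analysis will be performed to compare time-to-death between the groups". That sentence is silent on how the matched sets enter the model. Stratification or robust variance is a detail that an article commonly leaves to the full plan, so no fault can be drawn from the silence.

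**Conclusion.** The point holds in a limited form. The named cost tests do not fit 150 patients against 600 matched controls without a reduction rule that the article does not give. The consequence depends on the rule: a 1.26-fold standard error with one control per patient; about 21.5% type I error if 600 pairs were treated as independent; and, with set means, a roughly valid t-test (4-7%) but a signed-rank test that rejects a true null in about 18% to 80% of simulated trials. The signed-rank test also does not estimate the mean cost difference, which is the natural measure for a cost comparison.

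The variance ratios rest on 1:4 sets, equal variances and a common within-set correlation. The signed-rank figures rest on assumed lognormal costs, because the article gives no cost distribution.

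Severity is moderate. Cost is one of several secondary objectives, and the Module 1 analysis plan treats secondary hypotheses as exploratory. The primary quality-of-life comparison is untouched.

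**What to change.** In Module 2, Statistical analysis plan, replace the pair tests by a regression of monthly cost on group that uses all controls, with the matched set as the cluster. A GEE, or a linear model or GLM with set-robust standard errors, would serve. Report the mean cost difference with a 95% CI, for example from a bootstrap that resamples whole matched sets. If a log link is used, the group coefficient is a cost ratio, so the difference must be derived from the predicted group means. Drop the signed-rank alternative. State the matching ratio in words, so that the set structure no longer has to be inferred.

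The cost is a few sentences in the plan and a little more analysis work. No new data are needed.

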### Module 3: qualitative analyses of SCN project diaries

#### Design and participants

The qualitative analyses of project diaries provide important insights into the work of the SCNs. The nurses will be asked to record their feedback concerning positive aspects of the OSCAR program, as well as opportunities for further improvements with regard to the transferability of OSCAR to the regular healthcare system. For each patient, the SCNs will record the number of additional consultations between two planned monthly consultations, and any recommendations to visit partners in their supply network.

#### Analysis plan

The following aspects are of interest for the qualitative content analysis: acceptance of OSCAR among the patients and among the participating hospitals; number of additional consultations for patients; subjective feedback and reasons for early program termination by the patient; barriers to consultations.

## Discussion

This study aims to evaluate whether the OSCAR program can improve quality of life for patients with advanced cancers and a poor prognosis by enhancing health literacy and participation in therapy planning through continued supportive care from an SCN. A variety of approaches currently exist for developing and evaluating navigation programs for cancer patients. One example is the *Onkolotse* project from the Saxon Cancer Society. It involves certified nurses, psychologists, and social workers, who having contact with cancer patients about 20 times within 1 year. The evaluation of this project focuses on the number of hospital admissions and psychological stress [8]. Nurses from the non-profit association Group Health contact patients weekly via telephone, and meet with them face-to-face at least once [26]. The nurses aim to develop strategies that address distress and focus on quality of life. In another project, experienced nurses attempt to identify patient needs with three different assessment tools and personal conversations [27]. The endpoints in this study are e.g. patient satisfaction, acceptance of the nurses’ advice, and the use of support services for cancer.

Nevertheless, there is a lack of implementation of these approaches in Germany. OSCAR was developed to provide patients with a year of regular support in matters regarding their cancer. This is a useful addition to existing structures such as the social services provided by hospitals, which address the immediate needs of patients after hospital discharge. Improving the continuity of care and building patient competences are important for cancer patients in a fragmented healthcare system. Moreover, suitable healthcare structures and contract frameworks are necessary for delivering low-threshold access to palliative care and supporting consultations.

Experiences gathered with OSCAR could be transferred to other chronic somatic diseases which are associated with severe physical and psychological distress in patients and their relatives.

One advantage of the evaluation is the mixed-method design, which includes patient-reported outcomes, claims data from health insurance funds, and qualitative analyses of the SCNs’ project diaries. To evaluate the effects of continuous SCN support in Module 1, a prospective, non-randomized, multicenter, longitudinal study design was applied. Our patients were not assigned randomly, due to the limitation of the SCNs, who were trained and supported by the BKK insurance fund. Since randomization was not carried out, we are concerned about selection bias. Therefore, the baseline characteristics will be compared and we will control for baseline imbalance by using propensity score in our analysis. The propensity score with the inverse probability of treatment weighting (IPTW) method will be applied because the results from this method are similar to a randomized trial [23, 24]. For Module 2, we will match the intervention and control cases in order to reduce bias and confounding factors as much as possible. Moreover, given the severity of the patients’ conditions, we aimed to reduce the interview time by using the short versions of the instruments, if available, rather than applying generic instruments. In conclusion, we believe our study provides healthcare support for cancer patients. Hopefully, it can be applied for other severe chronic diseases. The evaluation of OSCAR is currently ongoing. In terms of providing healthcare support according to the patient’s needs, we expect our study to show that SCN support has a positive effect on the patient’s quality of life, health literacy, and participation in therapy planning.

